Moreover, a 2018 review found that adults spend approximately 8 hours participating in sedentary behavior (SB) daily [7]. SB is characterized by EE less than or equal to 1.5 metabolic equivalents of task (MET), with the Sedentary Behavior Research Network further detailing in 2017 that SB occurs while in a seated, reclined, or lying posture [8]. Emerging evidence indicates that excessive SB participation is associated with an increased prevalence of cardiometabolic diseases and risk of all-cause mortality [9] while reducing SB participation and subsequently increasing PA participation—even to a light-intensity—can significantly improve BMI and diastolic and systolic blood pressure (BP) [10-12]. Additionally, while intermittent standing bouts may be a feasible approach to reduce prolonged sitting, reclining, or lying through a postural change, passive or “idle” standing produces limited bodily movement, typically remaining below the 1.5 MET threshold to classify as light-intensity physical activity (LPA) [13].

Thus, reducing stationary behavior (ie, SB and idle standing) is a public health challenge that should be addressed through movement behaviors that reach MET thresholds at or above an LPA level. While specific LPA guidelines have yet to be established, the WHO advises adults to minimize SB time and substitute that time with any type and intensity of PA, including LPA [5]. Given that walking is generally feasible and accessible for adults who ambulate [5,14], it can serve as an ideal mode for not only replacing stationary behavior with LPA participation but also meeting WHO MVPA recommendations [5,14,15]. Walking paces around 0.82-0.89 m/s can exceed the 1.5 MET threshold for LPA [16,17]. To achieve the MPA threshold, walking must be performed at faster paces, typically around 1.3-1.8 m/s [16]. Since the 2020 WHO recommendations recognize that every minute of MVPA—regardless of bout duration—contributes toward an individual’s weekly targets [5], promoting walking behavior at faster paces may be an appropriate approach to increasing weekly MVPA volume while also breaking up stationary behavior.

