### Objective, Aims, and Research Questions

This protocol paper presents the development of the “Walking With Just-in-Time Adaptive Interventions” (WWJ) iPhone and AW app, server, and methodology for a 6-week pilot study among adults who are not meeting the 2020 WHO PA recommendations. The primary aims of the WWJ’s study are to examine the feasibility and initial impact of a 2-week JITAI approach for increasing walking behavior (ie, walking speed, distance, and duration) and decreasing stationary behavior (ie, duration of SB and idle standing) compared to a 2-week baseline observation period and a 2-week just-in-time learning period. Thus, our corresponding research questions include: (1) Is the WWJ feasible, regarding recruitment, retention, intervention fidelity, acceptability, adherence, and engagement? (2) To what extent does the just-in-time approach impact walking and stationary behavior compared to baseline? (3) How do changes in walking and stationary behaviors across a 2-week just-in-time and a 2-week JITAI approach compare to baseline?

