**Figure 3 figure3:**
[figure not shown]
The WWJ intervention notifications: walk faster, walk longer, and stand up. WWJ: Walking With Just-in-Time Adaptive Intervention.

The learner module (Figure 2) also establishes baseline walking and stationary behaviors during the initial 2-week observation period by passively monitoring behaviors and calculating their applicable averages (eg, average walking speed) per bout. During the just-in-time learning period, intervention notifications are triggered at each instance that participants meet a predetermined threshold for walking and stationary behaviors—unless they have marked themselves as “busy” on their calendar to not burden the user during unsuitable times such as work meetings. The threshold for the walking notifications is set at 250 m from the initial start point of a walking detection. This distance was chosen after trial-and-error field testing among 4 authors ([name], AV, KD, and [name]), which indicated that walking less than 250 m from a given starting location may not align with viable opportunities to walk faster or longer. The WWJ application will send a “walk longer” notification if the system recognizes that the user is in or near a previously tagged location. In all other cases, participants will receive a “walk faster” notification. When stationary behavior is detected for 30 continuous minutes, the application will send the “stand up and move around” notification. The system will determine if these interventions are successful or not (ie, receptiveness) either by comparing the current behaviors in the just-in-time learning period to those in the observation period within the same contexts for walking behavior or by the AW detecting that the user got up and walked around for a minute for stationary behavior. As shown in Figure 2, data collected by the executor during the just-in-time learning period serves as labeled training data to compute and optimize personalized prompting policies for the JITAI period. At the end of the just-in-time learning period, the learner module uses this labeled data to generate a decision-tree–based policy, predicting when and when not to send the intervention notifications to the user based on their current context, past receptiveness, and predicted support needs. As predicting behavior is uncertain, the learning model will deliberately use intervention notifications even if the user may not be receptive, with a 10% chance of such occurrences, to allow behavior change in previously nonoptimal contexts and for the system to learn continually.

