##### Walking and Stationary Behaviors

Our WWJ app will collect timestamped walking and stationary behaviors once respective thresholds are met (described previously in the Architecture of the WWJ App and Server section). The Apple watchOS behavior detection APIs use its combined location sensors—the GPS, the Globalnaya Navigatsionnaya Sputnikovaya Sistema, Galileo, and Quasi-Zenith Satellite System—and its motion sensors—triaxial accelerometer and gyroscope—to detect walking and stationary behaviors via Apple’s proprietary algorithms. These walking behaviors will include duration to the nearest whole second, distance to the nearest meter, and speed calculated from the collected distance divided by duration to the nearest meter per second. In addition, when a walking bout is detected, HR will be collected every 10 seconds. The duration of stationary behavior will be recorded to the nearest whole second.

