### Analytic Plan, Sample Size, and Power Estimates

#### Data Processing

The WWJ server will store all data for manual processing. Data processing will start by ensuring all timestamps for walking and stationary bouts are sequentially aligned. This alignment will allow for accurate calculations for transitions between these states and other activity modes. Outliers, including device-specific artifacts, such as overlapping timestamps and erroneous bout durations such as those too short to be meaningful (eg, <10 seconds) or exceeding physical limits (eg, >5 hours of continuous walking) and walking speeds surpassing human capacities (eg, >3 m/s) [40], will be identified and reviewed for manual correction or exclusion. Additionally, geographic locations tagged in the data and any nonadherence responses marked as “other” and inputted by participants will be downloaded and coded using an inductive approach to group similar entries into cohesive categories emerging organically from the data. Once fully processed, all data will be stored in a standardized format.

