#### Analytic Plan

Using the latest version of JMP Statistical Software (currently JMP, version 19.01, SAS Institute Inc, 1989-2025), preliminary analyses will include baseline descriptive statistics and exploratory data analysis. Baseline characteristics of the participants (eg, self-reported MVPA minutes from the screener, demographics, behavior change constructs, anthropometrics, and resting vital signs); recruitment, enrollment, and retention rates; implementation fidelity; adherence and compliance rates; user-burden; acceptability; treatment-specific expectations of benefits and preferences will be summarized in frequency tables for categorical variables and means and SDs for quantitative variables. Qualitative responses to applicable feasibility notifications and open-ended exit surveys will be explored.

Walking behavior and stationary time measures through all 3 periods—baseline, just-in-time, and JITAI—support a 1-way within-subjects ANOVA analysis of continuous measures (eg, average bout duration, speed, distance, and stationary time per study period for each participant) to demonstrate the feasibility of effecting a change in the behavior profile throughout the WWJ study. The intended 1-way within-subjects ANOVA assumes limited outliers, normality, and sphericity, which will be assessed graphically using boxplots, the Shapiro-Wilk test, and Mauchly test, respectively. Outliers, if present, will be assessed for their potential to weaken the analysis and removed if necessary. Nonnormal data will be transformed using the Box-Cox procedure to achieve normality. If sphericity is violated, the Greenhouse-Geisser and Huynh-Feldt corrections will be used. Tukey post hoc testing will be used to explain the differences between WWJ periods. If normality cannot be approximately achieved, the nonparametric Friedman test will be used. The model will be extended to allow for covariates if data screening of other collected demographic measures (eg, education) suggests their importance.

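### Walking speed is specified to the nearest 1 m/s, too coarse for the protocol's own walking paces; if bout speeds rounded this way enter the period analysis, measured change and power for speed are distorted

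*Protocol article*

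**What the plan says.** Under Objective, Aims, and Research Questions, the primary aims include "increasing walking behavior (ie, walking speed, distance, and duration"), so speed is a named outcome. Under Walking and Stationary Behaviors, the resolution of the three bout-level fields is fixed. For speed the rule is "speed calculated from the collected distance divided by duration to the nearest meter per second". The two fields from which it is derived are kept much more finely: "duration to the nearest whole second, distance to the nearest meter". No other section gives a finer resolution for speed.

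The Background supplies the reference paces. For light intensity: "Walking paces around 0.82-0.89 m/s can exceed the 1.5 MET threshold for LPA". For moderate intensity, "walking must be performed at faster paces, typically around 1.3-1.8 m/s".

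The Analytic Plan treats as continuous ANOVA variables the "average bout duration, speed, distance, and stationary time per study period for each participant". Data Processing flags "walking speeds surpassing human capacities (eg, >3 m/s") for review. The Architecture section says that the learner keeps baseline averages, average walking speed among them. It also says that walking prompts are judged against observation-period behavior in the same contexts, without naming the metric or a cut-off.

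**The concern.** A one-unit grid is wide compared with the whole range of human walking speed. Every speed from 0.5 to just under 2.5 m/s is stored as 1 or 2, so for a single bout the recorded speed amounts to an indicator of whether the pace reached 1.5 m/s. Realistic changes in pace are a fraction of a unit: most are recorded as zero, and those that happen to cross 1.5 m/s are recorded as a full unit.

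At stake is one of the named walking outcomes. If rounded bouts are averaged into the period means, a participant's measured change reflects the distance of the usual pace from 1.5 m/s as well as the true change, and the planned power does not carry over to speed. The loss is avoidable, because speed is derived from two fields that are kept at fine resolution.

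**Working it through.** **1. The plan's own power figure.** Inputs from Sample Size and Power Estimates: n = 17, m = 3 periods, correlation 0.5, f = 0.32, alpha 0.05.

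- Noncentrality: lambda = f² × n × m / (1 − rho) = 0.1024 × 17 × 3 / 0.5 = 10.44.
- Degrees of freedom: 2 and 32; critical F = 3.29.
- Power = 0.794 at n = 17 (0.820 at n = 18); 17 / 0.85 = 20.

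The stated 17 and 20 are reproduced. The sample-size arithmetic is not in question.

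**2. The cited paces on a 1 m/s grid** (no assumptions needed).

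| True pace (m/s) | Stored as |
|---|---|
| 0.82-0.89 (light) | 1 |
| 1.30-1.49 (moderate, lower part) | 1 |
| 1.50-1.80 (moderate, upper part) | 2 |
| 3.00-3.49 (above the cleaning limit, apart from 3.00 itself) | 3 |

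The part of the moderate range that cannot be told from light pace is (1.50 − 1.30) / (1.80 − 1.30) = 0.4, or two-fifths. A bout going from 0.82 to 1.49 shows a change of 0; one going from 1.49 to 1.51 shows a change of 1. If the 3 m/s limit is applied to the stored value, speeds up to 3.49 pass it.

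**3. Resolution available from the stored fields.** Take a walk at the notification threshold ("The threshold for the walking notifications is set at 250 m from the initial start point of a walking detection"), with distance off by 0.5 m and duration by 0.5 s in opposite directions:

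- 250 m in 208 s: 250.5 / 207.5 − 250 / 208 = 0.005 m/s.
- 250 m in 278 s: 250.5 / 277.5 − 250 / 278 = 0.003 m/s.

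Rounding to 1 m/s allows an error of up to 0.5 m/s.

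**4. Effect on a mean of rounded bouts.** For bout speeds that are normal with mean mu and SD s, the expected stored value is the sum over k = 1, 2, 3, … of 1 − Φ((k − 0.5 − mu) / s). Example with s = 0.20: mu = 1.2 gives 0.9998 + 0.0668 = 1.067, and mu = 1.3 gives 1.0000 + 0.1587 = 1.159. A true gain of 0.10 is then recorded as 0.092. Other settings for the same true gain:

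| Start pace (m/s) | Bout SD (m/s) | Recorded gain (m/s) |
|---|---|---|
| 1.0 | 0.10 | 0.000 |
| 1.2 | 0.10 | 0.021 |
| 1.2 | 0.25-0.30 | 0.099-0.100 |
| 1.45 | 0.10 | 0.383 |

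The distortion is severe when bouts vary little, and nearly absent at some paces when they vary a lot.

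**5. Effect on ANOVA power.** From the plan: n = 17, f = 0.32, correlation 0.5. Assumed, because the article gives none of these: SD of participants' speeds 0.2 m/s, 30 bouts per period, usual pace 1.0-1.3 m/s, bout SD as shown. The SD of the three period means is f × 0.2 = 0.064. That is a true change of 0.064 / (√2 / 3) = 0.136 m/s if the whole gain comes after baseline and is then held, or 2 × 0.064 / √(2/3) = 0.157 m/s if it is linear over the three periods. Simulated repeated-measures ANOVA on period means of rounded bouts gives:

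| Bout SD (m/s) | Power, bouts rounded to 1 m/s |
|---|---|
| 0.10-0.15 | about 0.10-0.68 |
| 0.20 | about 0.56-0.70 |
| 0.25-0.30 | about 0.64-0.75 |
| Unrounded speed | about 0.79 |

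Within each row, power is lowest at a usual pace of 1.0 m/s and tends to rise toward 1.3, most steeply at the small bout SDs. At bout SD 0.10-0.15, the true change of 0.136-0.157 m/s is recorded as about 0.05-0.24 m/s.

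**The case against.** The phrase may be loose wording for the unit. The Weather section uses the same formula for precipitation to the inch, which is hardly a literal resolution, and elsewhere speed is quoted to 0.01 m/s and treated as a continuous variable that may need a Box-Cox transformation. This reading remains possible. Against it, the same sentence uses the phrase as a true resolution for seconds and meters, and a reader who follows the text would round. It needs correcting on either reading.

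Averaging over bouts dithers the rounding and recovers much of the signal. This stands: at a bout SD of 0.25-0.30 m/s most of the power survives. It would therefore be too strong to infer that realistic gains are erased or exaggerated in general; that holds in only part of the plausible range.

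The article does not say that the rounded value enters the analysis, so the power loss is conditional on that. A reader might also suppose that the period mean itself is rounded, which would do more damage, but the resolution is stated for collected bout behavior and nothing extends it to period averages.

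A reader might further infer that walk-faster prompts were mis-scored and the trees badly trained. If success meant exceeding the baseline average on rounded speed, a true 10% gain at 1.0-1.1 m/s and bout SD 0.10-0.20 would count as success in 0-7% of bouts rather than 69-86%. Both conditions are supplied by the reader: the Architecture section states neither the metric nor the resolution.

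Finally, the 3 m/s limit is given as an example that triggers manual review, so its failure on the rounded scale is minor.

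**Conclusion.** As written, the speed resolution is wrong for its purpose. At bout level this follows from the article's own paces alone: light pace and the lower two-fifths of the moderate range share one stored value. At the level of the ANOVA the harm is conditional on rounded bouts being averaged, and its size depends on a bout SD that the article does not give: from near-total loss of power when bouts are uniform and the usual pace is about 1.0 m/s, to a loss of a few points when bouts vary widely. Effects on prompt labels and decision trees cannot be established from the document. The planned sample size and the analyses of distance, duration and stationary time are not affected. Because meters and seconds are stored and the Results section describes the analyses as not yet complete, the outcome analysis can be put right in full. Only labels that the app may already have produced from rounded speed could not be undone.

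**What to change.** In Walking and Stationary Behaviors, replace the 1 m/s resolution with speed computed from the stored meters and seconds and kept to at least 0.01 m/s. Use that value for the bout and period averages and for the 3 m/s check.

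State which speed, at what resolution, the app used to label walk-faster success. If it was rounded, report success rescored on unrounded speed beside the app's labels, and note that the decision trees were trained on rounded labels.

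The cost is one line of text and a recalculation from stored fields; no new data are needed.

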##### Feasibility

The feasibility assessment of the WWJ pilot study will be guided by the recommendations outlined by National Institutes of Health’s National Center for Complementary and Integrative Health [37]. Key feasibility metrics will include rates of prospective participants screened per month, participants enrolled per month, retention of participants per study measure, fidelity for protocol delivery, and adherence to study protocol. In cases of nonadherence to the WWJ intervention notifications, a follow-up notification will be sent to the participant to inquire why the prompt was not followed [18]. Response options will include “I did not see the notification,” “I did not want to respond,” “It was not a good time,” and an option to choose “other” for inputted responses. Additionally, compliance with wearing AW for at least 10 hours each day for at least 4 hours each week will be determined. An exit survey will include perceived user burden with items adapted from the 2016 User Burden Scale developed by Suh et al [38], acceptability, treatment-specific expectations of benefits, and treatment-specific preferences for consideration for future iterations of WWJ to further detail user feedback [18].

### Protocol

#### Preintervention Visit and WWJ Application Set-Up

The preintervention visit will take place in a private room to explain study procedures and complete baseline assessments (ie, demographics, behavior change constructs, anthropometrics, and resting vital signs). The AW will be initialized according to the participant’s age, sex, race, weight, and height by inputting or updating these measures in the Apple Health app. Apple Health and Fitness notifications (eg, stand reminders, goal completions, daily coaching, special challenges, and activity sharing notifications) will be disabled. Participants will download the TestFlight application—an Apple Developer app that allows for testing beta versions of our WWJ iOS and watchOS apps—and be sent an invitation email with a code to access the WWJ app. Participants will be guided through the WWJ app installation on the AW and paired iPhone. After downloading, the WWJ app goes through each data type, including precise location, which will be monitored to obtain user approval. Location services for the WWJ app will be turned to “always on and precise.” To familiarize participants with the WWJ app, visually enhanced instructions on how to tag precise geographic locations on the AW, use the Apple Calendar to schedule busy times on the iPhone, and restart the WWJ app will be provided in paper and digital forms, and tasks will be demonstrated on a laboratory iPhone and AW.

#### WWJ Observation Period, Just-in-Time, and JITAI Periods

For the next six weeks, participants will be instructed to (1) wear the AW on their nondominant wrist during all waking hours, (2) charge the AW during nonwaking hours, (3) tag all locations visited, (4) input and update busy times daily, (5) restart the WWJ app every morning upon waking, and (6) respond to all WWJ app feasibility notifications. During the 2-week observation period, the WWJ app will only monitor walking and stationary behaviors without sending any feasibility or intervention notifications. During the 2-week just-in-time learning period, the WWJ app will (1) monitor walking and SBs, (2) send intervention and feasibility notifications across all appropriate contexts, and (3) assess participant receptiveness to the intervention notifications to begin training for each participant’s unique contexts in which intervention notifications led to successful (vs failed) behavioral changes. During the 2-week JITAI period, the WWJ app will (1) monitor walking and SBs and contextual variables; (2) send notifications at the most opportune moments based on the decision tree policy and the extent to which prior notifications were successful [39]; (3) assess participant receptiveness; and (4) elicit reasons for nonreceptiveness.

#### Postintervention Visit

The postintervention visit will take place in a private room to complete postassessments (ie, behavior change constructs, anthropometrics, and resting vital signs), uninstall the WWJ app, and assist the participant in restoring all original settings on their iPhone and AW. If an AW was borrowed for this study, the device will be returned at this time.

### Analytic Plan, Sample Size, and Power Estimates

#### Data Processing

The WWJ server will store all data for manual processing. Data processing will start by ensuring all timestamps for walking and stationary bouts are sequentially aligned. This alignment will allow for accurate calculations for transitions between these states and other activity modes. Outliers, including device-specific artifacts, such as overlapping timestamps and erroneous bout durations such as those too short to be meaningful (eg, <10 seconds) or exceeding physical limits (eg, >5 hours of continuous walking) and walking speeds surpassing human capacities (eg, >3 m/s) [40], will be identified and reviewed for manual correction or exclusion. Additionally, geographic locations tagged in the data and any nonadherence responses marked as “other” and inputted by participants will be downloaded and coded using an inductive approach to group similar entries into cohesive categories emerging organically from the data. Once fully processed, all data will be stored in a standardized format.

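### Stationary time is not tied to worn time and no stated rule separates non-wear from stillness, so a change in wear between periods can bias the contrast in either direction

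*Protocol article*

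**What the plan says.** Sample Size and Power Estimates names change in walking behavior and in stationary time as the primary outcomes. The Analytic Plan puts per-participant measures into a within-subjects ANOVA, for example "average bout duration, speed, distance, and stationary time per study period for each participant". No wear-time denominator is stated.

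Data Processing lists overlapping timestamps, "erroneous bout durations such as those too short to be meaningful (eg, <10 seconds"), bouts "exceeding physical limits (eg, >5 hours of continuous walking") and "walking speeds surpassing human capacities (eg, >3 m/s"). These records "will be identified and reviewed for manual correction or exclusion". Non-wear, charging and long stationary spells are not among the examples.

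Under Walking and Stationary Behaviors, both states come from location and motion sensors through a proprietary algorithm. Heart rate is described for walking only: "when a walking bout is detected, HR will be collected every 10 seconds". The instructions for the six weeks tell participants to wear the watch during all waking hours and to "charge the AW during nonwaking hours".

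Wear time appears under Feasibility: "compliance with wearing AW for at least 10 hours each day for at least 4 hours each week will be determined". The Analytic Plan lists compliance among the quantities to be summarised and does not connect it to the stationary outcome.

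**The concern.** A watch can record stillness because the wearer is sitting or because nobody is wearing it. The article gives several artifact rules and promises a wear measure, but does not use that measure to define the outcome. A total of stationary time then depends on how long the watch was worn as well as on behaviour.

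This matters because the periods run in a fixed order without a concurrent control. The observation period sends no notifications and the two later periods do. Strengths and Limitations itself raises possible burnout or disengagement over time. If wear changes for that reason, the change coincides with the contrast being tested.

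There is a possible second effect. Thirty continuous stationary minutes trigger a stand-up prompt, and success requires the watch to detect about a minute of walking. If an unworn watch registers as stationary, prompts sent to it would count as failures. Those failures would enter both the labels that train the decision trees and the secondary success rates.

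**Working it through.** The plan gives no figure for non-wear, so there is none to reproduce. The sample-size figure is not in question here.

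**Inputs.** About 8 h/day of sedentary time is cited in the Background. The following are assumptions: a 16 h waking day (so the sedentary share is s = 8/16 = 0.5), wear W of 12 to 14 h/day, the same sedentary share in worn and unworn time, all worn sedentary time logged, and stationary time analysed as a total. The share g of unworn waking time that is logged as stationary is unknown and is varied from 0 to 1.

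**Formula.** Recorded stationary time = s × W + g × (16 − W) hours per day.

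**1. Wear falls from 14 to 12 h/day, no change in behaviour**

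| g | W = 14 | W = 12 | Change |
|---|---|---|---|
| 1 | 7 + 2 = 9 h | 6 + 4 = 10 h | +60 min |
| 0.5 | 7 + 1 = 8 h | 6 + 2 = 8 h | 0 |
| 0 | 7 h | 6 h | −60 min |

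The change is (g − s) × 2 h, so it is zero only when g equals the sedentary share.

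**2. True reduction of 30 min/day (480 to 450 min, s from 0.5 to 450/960 = 0.46875)**

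- Wear constant at 14 h: 0.46875 × 840 − 0.5 × 840 = −26 min for any g.
- Wear 14 to 13 h: +6 min at g = 1 (sign reversed), −24 at g = 0.5, −54 at g = 0.
- Wear 12 to 14 h: −86 at g = 1, −26 at g = 0.5, +34 at g = 0 (sign reversed).
- Break-even at g = 1: later wear = 840 × 0.5/(1 − 0.46875) = 790.6 min. A loss of about 49 min/day of wear hides the whole reduction.

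For scale, if each half-hour of 8 stationary hours produced the one prompted minute, the direct effect would be 8 × 2 × 1 = 16 min/day.

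**3. Average bout duration, only if unworn spells are logged as stationary**

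- Level: ten spells totalling 480 min average 48 min. Adding one 480-min charging spell gives 960/11 = 87.3 min.
- Constant charging does not cancel in a mean. If ten spells become twelve of 40 min (still 480 min), the true change is −8 min. With one 480-min charging spell in each period it is 960/13 − 960/11 = 73.8 − 87.3 = −13.4 min.
- Unequal non-wear can reverse the sign. Take 168 spells per period averaging 40 then 38 min, with two 480-min unworn spells at baseline and four later: (6,720 + 960)/170 = 45.2 and (6,384 + 1,920)/172 = 48.3. The change is +3.1 min against a true −2.

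**The case against.** The article does not describe what the detection algorithm records off the wrist. The Analytic Plan expects poor adherence to produce missing observations, to be explored and handled by a mixed model. The cleaning list is open-ended and followed by manual review, so a long stationary spell could be caught. A wear metric is promised, which implies some wear signal, and the app's main screen shows heart rate beside the current state, so heart rate may not be confined to walking. The wear instruction is the same throughout, overnight charging that is equal in every period largely cancels in a difference of totals, and the app is restarted each morning. Non-wear algorithms are also often left to an analysis plan.

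Much of this stands. A reader might infer that non-wear does enter stationary time and that falling wear makes behaviour look worse. The document does not support that reading: it requires g near 1, which is stated nowhere, and at g = 0 the bias runs the other way. Nor does the article say that wear will change.

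Three points remain. If unworn time is simply not logged, an unscaled total still moves with wear. The mixed model deals with absent observations, not with a partly worn day that yields a value. And a motionless spell of eight hours breaches no physical limit, so the stated examples do not clearly lead a data reviewer to remove it.

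**Conclusion.** The point holds in conditional form. The plan names an unscaled stationary-time outcome, gives no criterion separating non-wear or charging from stillness, and confines wear time to feasibility. A between-period change in wear can therefore bias this primary contrast, with a direction the article leaves unknown. Under the assumed values, a two-hour fall in wear shifts recorded stationary time by anything from −60 to +60 min/day. That is large beside the 16 min/day direct prompt effect, and the shift vanishes only if about half of unworn time is logged as stationary. The effects on bout duration and on prompt success rates arise only if unworn time is logged as stationary.

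The wear metric cannot serve as a valid-day rule as written, because a single day meeting its daily figure already exceeds its weekly one. The matter should be settled before analysis. The Results section says data collection is complete and analyses are pending.

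**What to change.** - In Data Processing, state how non-wear and charging are identified, from stored device state or from whatever signal supports the wear metric, and remove that time. State also whether unworn time is logged as stationary.
- Where no such signal exists, exclude stationary spells above a fixed length as a sensitivity analysis.
- In the Analytic Plan, analyse stationary time as a share of worn waking time, and report worn hours by period.
- Exclude prompts issued during identified non-wear from the success rates.
- Reconcile the daily and weekly figures in the wear-compliance statement under Feasibility so that it gives a usable valid-day definition.

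The cost is processing and analysis-plan wording, with no new data if device state or another wear signal was stored. The downside is that some true long sitting spells or ambiguous time may be dropped. Failure labels already used to train the decision trees cannot be changed now.
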